### Randomisation and allocation

Participants will be randomly allocated into the intervention and control groups in a 1:1 ratio. The allocation sequence to either group will be generated using computer‐generated random numbers, ensuring that the assignment of participants to either the intervention group or the control group is entirely random and unbiased (Figure 1).

**Figure 1 jeo270034-fig-0001:**
[figure not shown]
Participant recruitment, randomisation and group allocation flowchart. 1‐RM, one‐repetition maximum; BFR, blood flow restriction.

### Intervention and blood sample collection

A multidisciplinary medical team led by the principal investigator will conduct the intervention in an ISO:9001‐certified laboratory (Laboratorio Avilab) (Table 4). Before the intervention, participants will have a pre‐exercise peripheral vein catheterisation, blood sample draw and PRP preparation for baseline measurements. Each participant will undergo standard venipuncture in the antecubital fossa by a single phlebotomist under sterile conditions for a total blood draw of 15 mL in a vacutainer and undergo a single centrifugation at 1500 rpm for 5 min. The plasma portion and buffy coat will be separated under direct visualisation with automatic pipettes from the red blood cells, and samples will be sent to the laboratory and divided into two aliquots, one for cell counts (automated cell counter), the other for IGF‐1 and IL‐6 immunoassays analysis within 6 h.

**Table 4 jeo270034-tbl-0004:** Summary of procedural steps during the test day.

**Procedural steps** Evaluation of eligibility in athletes undergoing routine screening, including Tegner Activity Scale assessment. Informed consent. Demographic data collection. Preblood flow restriction blood sample collection. Low‐load blood flow restriction bilateral knee extension intervention. Postblood flow restriction blood sample collection at 10', 20' and 30'. Laboratory testing of collected samples.

The participant will then perform the low‐load BFR protocol. The low‐load bilateral knee extensions under BFR (using tourniquets at the proximal end of both thighs) will follow the standard protocol of four sets consisting of 30‐15‐15‐15 repetitions, with 30‐s rest intervals at 80% of limb occlusive pressure (calculated using arteria pedis ultrasound) and 30% of 1‐RM load (using Holten diagram).

A staff physician will monitor the entire exercise protocol and recovery period for safety and adverse events. Once the exercise protocol is completed, participants will be allowed a recovery period (including rest, walking if desired, and fluid intake) before undergoing the consecutive blood draw. The maximum recovery permitted time will be 5 min. The subsequent blood draws and PRP processing will be performed identically to the first at 10‐, 20‐ and 30‐min postintervention. The average test participation will last around 2 h.

### Outcome assessment

Measurements will be taken before and 10, 20 and 30 min after the intervention. The primary outcomes of this study are directly related to the hypothesised benefits of BFR‐enhanced PRP. The expected result is that the standard protocol of low‐load bilateral knee extensions under BFR will increase the platelet and leucocyte count, IGF‐1 and IL‐6 in the PRP preparation. Increases in platelet and leucocyte counts and elevated IGF‐1 and IL‐6 concentrations within the first 30 min after the exercise bout could indicate enhanced healing and anti‐inflammatory effects that could be translated into an office setting, potentially leading to improved outcomes in musculoskeletal pathologies.

The study's data quality relies on standardised procedures and thorough research team training. This includes the utilisation of a single phlebotomist for all blood draws, the oversight of the principal investigator during the exercise protocol and two certified bioanalysts to individually handle IGF‐1 and IL‐6 measurements. The XS‐i Fluorescent Flow Cytometer (Sysmex) will be employed for leucocyte differential analysis, providing essential information on the various types of white blood cells. The XS‐i Automated Hematology Analyzer (Sysmex) will be used for electrical impedance analysis, measuring platelet, red cell and leucocyte counts. The Finecare FIA Meter Plus Analyzer (Wondfo) will conduct fluorescence immunochromatographic analysis of IL‐6, a significant biomarker in this research. The LIAISON Analyzer (DiaSorin) will also perform IGF‐1 chemiluminescence testing, which is crucial for measuring IGF‐1 levels. The implemented BFR System (The Occlusion Cuff Pro®) is specifically designed to apply BFR during the exercise protocol, ensuring accurate and consistent application of BFR across all participants.

### Benefits/risks

Patients will benefit from the systemic and local musculoskeletal effects of BFR training and receive their blood test results for annual control.

BFR training is safe, with risks consistent with traditional exercise modalities [22]. However, sparse reports of common side effects include pain or discomfort during exercise, delayed‐onset muscle soreness and cardiac stress (increased heart rate, increased blood pressure, decreased stroke volume). In contrast, more serious, less common side effects include numbness or nerve injury, bruising or ischaemic injury, dizziness or fainting, thrombus formation, muscle damage and rhabdomyolysis. These risks are negligible when BFR is performed under current standards.

Contraindications for BFR implementation include a history of or the potential for deep vein thrombosis, blood clotting disorder, poor circulation, hypertension, inadequate function of the lymphatic system, history of endothelial dysfunction, varicose veins, peripheral vascular disease, diabetes, easy bruising, active infection, cancer, renal compromise, pregnancy and intervention intolerance.

Potential adverse effects will be recorded in a logbook and promptly reported to the Research and Bioethics Committee. A follow‐up call will be done 72 h after the blood sample collection to assess for late presentation of any adverse effects.

### Data integrity

The medical record numbers will be paired with a unique research identification number and stored on a separate spreadsheet to protect against a breach of privacy. Data storage includes secure electronic storage with restricted access, regular data backups and compliance with data protection regulations. Also, the link between code and identifier will be destroyed after the study is finished, and de‐identified data will be kept for at least 5 years. The principal investigator will monitor the data collected, including those related to unanticipated problems and adverse events. Any complications that arise during the trial must be reported immediately. In the event of data breaches, these should be reported to the project coordinator within 24 h of the incident being identified, ensuring prompt action to mitigate potential risks.

### Statistical analyses

The study will involve a sample size of 22 patients. This sample size has been validated by a power analysis, which anticipates a 25% increase in IGF‐1 with a significance level (α) of 0.05 and 80% statistical power. Additionally, previous studies have been conducted using a similar sample size [18, 24, 53].

Patient data will be summarised using the following descriptive statistics: mean and standard deviation, median and interquartile range and/or frequency and percentage (%). The distribution of numerical variables will be assessed using the Shapiro–Wilk test. For numerical variables, the repeated‐measures analysis of variance test will be used for those with a normal distribution, and the Friedman test will be used for those with a nonnormal distribution. Values of *p* < 0.05 will be considered statistically significant. Statistical analysis will be performed using SPSS version 19 and Microsoft® Excel® version 2016.

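### Repeated-measures ANOVA is named without a baseline covariate although every participant has a pre-exercise value; adjusting for it costs almost nothing, with a gain that depends on the unstated correlation and effect size

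*Protocol article*

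**What the plan says.** Under Outcome assessment: "Measurements will be taken before and 10, 20 and 30 min after the intervention". The intervention section confirms that each participant has blood drawn and PRP prepared before exercise to give baseline measurements.

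Under Statistical analyses, the test for normally distributed numerical variables is repeated-measures ANOVA (the "analysis of variance test will be used for those with a normal distribution"), with the Friedman test otherwise. No covariate, change score, group factor, group-by-time term or contrast is named.

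On size: "The study will involve a sample size of 22 patients", and under Randomisation and allocation: "Participants will be randomly allocated into the intervention and control groups in a 1:1 ratio". That makes at most 11 per arm, because participants with missing data are dropped. The calculation is one "which anticipates a 25% increase in" IGF-1, at a significance level "of 0.05 and 80% statistical power". No SD, no correlation between draws and no powered test is given.

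**The concern.** With four measurement times and a plain repeated-measures ANOVA, the natural reading is that the pre-exercise value is one of four levels of time. Baseline then serves only as part of the outcome. The group-by-time term makes an implicit change-from-baseline comparison, which is less efficient than covariate adjustment unless the correlation between draws is very high. It also spreads its power over three degrees of freedom.

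With 11 men per arm, chance baseline differences in IGF-1 or cell counts can be sizeable. Randomisation makes this a matter of precision, not of bias. What is at stake is power that the trial could have from data it already collects.

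**Working it through.** **The plan's own figure.** N = 22 cannot be reproduced, because no SD is given. For a two-sided two-sample t-test with 11 per arm, 80% power needs a difference of 1.256 SD. A 25% increase then implies an SD of 25/1.256 = 19.9% of the mean. At an SD of 30% the power would be about 50%. So 22 is attainable under some SDs and is not shown to be wrong, but it gives no anchor for the gain.

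**Inputs.** From the protocol: n = 11 per arm, four times, alpha 0.05 (two-sided assumed). Assumed: SD 1 at each time, equal correlation ρ between any two draws, and an effect of 0.8 SD. An effect of 0.8 SD matches a 25% increase if the SD is 25/0.8 = 31% of the mean.

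**Formulas.** For group effects e(t) at the four times, with mean ē:
- Group-by-time test: noncentrality (n/2)·Σ(e(t) − ē)²/(1 − ρ), on 3 and 60 df.
- Mean post value minus baseline: variance 4(1 − ρ)/3, on 1 and 20 df.
- Mean post value adjusted for baseline: variance (1 − ρ)(1 + 3ρ)/3, on 1 and 19 df.
- Variance ratio, change to adjusted: 4/(1 + 3ρ), which is 1.60 at ρ = 0.5, 1.29 at 0.7, 1.18 at 0.8 and 1.08 at 0.9.

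**Sustained effect, worked at ρ = 0.7.** The effects are 0, 0.8, 0.8, 0.8, so ē = 0.6 and the sum of squares is 0.36 + 3 × 0.04 = 0.48.
- Group-by-time: 5.5 × 0.48/0.30 = 8.8.
- Mean change: 5.5 × 0.64/0.40 = 8.8. This is the same signal on one degree of freedom instead of three.
- Adjusted: 5.5 × 0.64/0.31 = 11.4, before a small loss for chance baseline imbalance.

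Simulated power (the formulas agree to within about a point):

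| ρ | Group-by-time | Mean change | Adjusted mean post | Due to 1-df contrast | Due to covariate |
|---|---|---|---|---|---|
| 0.5 | 44% | 60% | 77% | 16 | 17 |
| 0.7 | 68% | 81% | 88% | 13 | 7 |
| 0.8 | 85% | 92% | 95% | 7 | 3 |
| 0.9 | 99% | 100% | 100% | 1 | 0 |

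**A larger effect.** At 1.256 SD, the value implied if N = 22 came from a two-sample t-test, the three powers are 85/93/99% at ρ = 0.5 and 98/99/100% at 0.7. The covariate's share falls to about 6 points and under 1 point.

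**Effect gone by 30 min.** The effects are 0, 0.8, 0.4, 0, so ē = 0.3 and the sum of squares is 0.09 + 0.25 + 0.01 + 0.09 = 0.44. At ρ = 0.7 the group-by-time noncentrality is 5.5 × 0.44/0.30 = 8.1. For the adjusted mean it is 5.5 × 0.16/0.31 = 2.8.

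| ρ | Group-by-time | Adjusted mean post | Loss |
|---|---|---|---|
| 0.5 | 40% | 28% | 12 |
| 0.7 | 63% | 35% | 28 |
| 0.8 | 81% | 44% | 37 |
| 0.9 | 99% | 70% | 29 |

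**Partial fading** (effects in proportion 1, 0.67, 0.33, with group-by-time set to 80%). The adjusted mean has 87% at ρ = 0.5, 79% at 0.7, 75% at 0.8 and 72% at 0.9.

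**The case against.** The strongest reply is that the article does not say baseline is a repeated level, that no covariate will enter, or which term will be read. A repeated-measures ANOVA can carry a covariate, and a fuller analysis plan may supply one. That stands as a limit on certainty. The method is nonetheless named here without a covariate, so the suggestion addresses a stated choice.

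It is also fair to say that this is a matter of efficiency, not error. In simulation under no effect, every method held about 5%. That stands too, and no figure in the protocol is contradicted.

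A reader might infer more than the documents support, in three ways:
- *That adjustment brings a large gain whatever the data.* The gain depends on a correlation and an effect size that the protocol does not give. At ρ of 0.8 to 0.9 the covariate adds little or nothing.
- *That the loss is as large as the gap to the group main effect.* A main effect averaged over all four times would include a baseline that cannot respond, and its variance would be 4/(3(1 − ρ)) times that of the adjusted contrast, or 4.4 at ρ = 0.7. Nothing says that this term will be read. The hypothesis concerns increases after exercise, which points to time or group-by-time.
- *That the average of the three post-exercise times must be the primary contrast.* The protocol assumes no time course. It looks only for increases within the first half hour, so a transient effect is not excluded.

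**Conclusion.** The point holds as a conditional recommendation. Baseline is available on everyone, the named test uses no baseline covariate, and for the same contrast adjustment did not lose to the change score in any scenario tabulated above. For a sustained 0.8 SD effect with 11 per arm, the covariate's own gain is about 17 points at ρ = 0.5, about 7 at 0.7 and 3 or fewer at 0.8 to 0.9. The rest of the gap to the group-by-time test is the benefit of a focused contrast. These figures rest on equal correlations, an assumed ρ and an assumed effect, and none of them can be tied to the protocol's stated "80% statistical power". Preferring the averaged contrast to group-by-time is a trade-off: it helps when the effect lasts and can cost up to 37 points when it has gone by 30 min.

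**What to change.** State in Statistical analyses that the between-group comparison uses the 10, 20 and 30 min values as the outcome, with the baseline value of the same outcome as a covariate, by ANCOVA or a mixed model. This takes one sentence and one residual degree of freedom, and needs no new data.

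As a separate decision, the sponsor should state which post-exercise comparison is primary (the average over the three times, or a test that allows the effect to vary over time) and what expected time course justifies it. Baseline adjustment is compatible with either. Any claimed power gain should be shown over a range of correlations, effect sizes and time courses.

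The sentence reaches only the ANOVA branch. The Friedman test takes neither a covariate nor a group factor, so that branch needs its own consideration.

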## DISCUSSION

The present randomised controlled trial aims to assess PRP changes in platelet and leucocyte count, IGF‐1 and IL‐6 concentration after bilateral low‐load knee extensions under BFR. The muscle metabolic stress induced by BFR has been associated with releasing IGF‐1 and IL‐6 into the bloodstream [9, 15, 31, 39, 40, 45, 49]. It can be performed safely [22] and implemented at a low cost in an office setting, making it an easy and fast intervention to potentially enhance PRP composition for treating sports‐related injuries.

Evidence of different PRP compositions targeting specific musculoskeletal pathologies is growing [13, 20, 25, 30, 41]. Leucocyte‐rich PRP preparations have been reported to be better in tendinopathies, while leucocyte‐poor are preferred for knee osteoarthritis [13, 20, 25, 30, 34, 41, 54]. The potential effects of BFR represent an exciting opportunity to increase the concentration of IGF‐1 and IL‐6 in PRP, with a synergistic effect that can benefit specific injuries like muscle injuries (hamstrings) and other cartilage and tendon pathologies. Literature on BFR implementation in major sports injury rehabilitation, such as ACL reconstruction [17, 32], is rapidly growing, and several authors have expressed its potential in treating muscle injuries [19, 28, 33].

With a BFR‐enhanced PRP formulation displaying a higher concentration of any or both IGF‐1 and IL‐6, there is an opportunity for treating muscle injuries [8, 29, 46, 52]. Although both molecules have been shown to contribute to musculoskeletal tissue healing, the chance to treat muscle injuries is the most exciting, as the current evidence on PRP has shown poor outcomes [7, 10, 11, 12]. The protocol allows the study of an enhanced PRP formulation for its potential implementation in multiple sports injuries.

## ETHICS STATEMENT

Ethical approval has been received from the Research and Bioethics Committee of Grupo Médico Vargas—Clínica Santa Sofía v.001‐2024 in February 2024. The trial has been prospectively registered with the BioMed Central—International Standard Randomised Controlled Trial Number (ISRCTN42221463).

## Data Availability

The data underlying this article are available in the article and its online supplementary material.
